#### Sample size

As to our knowledge there are no directly comparable published data, a sample size estimation was performed based on the results of a pilot study conducted at the L.O.O.P. GBF. During this pilot study, a single participant performed submaximal single-leg hopping at 2 Hz (using a metronome) for 30 seconds under five simulated gravity conditions (1, 0.5, 0.37, 0.25, 0.17g). For each session, peak vertical joint reaction forces were calculated for the hip, knee and ankle using the same simulation framework as described in this protocol (see *“Planned Data Analysis”)*.

Using this simulation framework, means and standard deviations of the peak vertical joint forces of the hip, knee and ankle were calculated and extracted for each gravity condition, which were used to calculate the Cohen’s *d* effect sizes based on the mean difference and pooled standard deviations [48]. These data were then used in an *a priori* power analysis to estimate a required sample size of 21 (S1 File) using G*Power (version 3.1.9) [49] with: t-test (matched pairs), α = 0.05, Power = 0.95, two-tailed. In order to ensure adequate data collection, we estimate a maximal data loss of 25%, therefore our sample size target will be 26 participants.

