### Planned statistical analysis

Statistical significance will be assumed at p < 0.05. Normality of the data will be assessed via Kolmogorov-Smirnov testing complemented by visual inspection of QQ plots and histograms. Normally distributed data will be presented as mean (±SD), non-normally distributed data will be presented as median (±IQR).

The effect of high-fidelity simulated gravity (1, 0.7, 0.5, 0.38, 0.27 and 0.16g) upon lower limb internal kinetics (i.e., joint reaction forces) when walking, running, and skipping at speeds ranging between 0.53–3.6 m/s will be determined by a Two-Way Repeated Measures ANOVA with:

Independent variables: six simulated gravity conditions; 10 locomotion trials (see Table 1)Dependent variables: Joint reaction forces of the hip, knee, and ankle

The effect of high-fidelity simulated gravity (1, 0.7, 0.5, 0.38, 0.27 and 0.16g) upon lower limb internal kinetics (i.e., joint reaction forces) during candidate plyometric movement (i.e., maximal ankle hopping, maximal effort countermovement jumping, and drop-jumps/landings) will be determined by a One-Way Repeated Measures ANOVA with:

Independent variables: six simulated gravity conditionsDependent variables: Joint reaction forces of the hip, knee and ankle

In case the assumption of sphericity has been violated–i.e., Mauchly’s test statistic is significant (p<0.05)–the Geisser-Greenhouse correction will be used to determine the effect of the independent variables on the dependent variables. If a significant effect of the simulated gravity condition, the locomotion trial, or the interaction between simulated gravity condition and locomotion trial is found, Bonferroni corrected post-hoc t-tests will be employed.

Alternatively, if data has a non-normal distribution the non-parametric Friedman test with Dunn’s post-test will be used.

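### The Friedman fallback fits the one-way plyometric analysis but cannot test the gravity-by-trial interaction planned for the two-way locomotion analysis, and its trigger is weak and under-specified

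*Protocol article*

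**What the plan says.** All of this stands in the protocol article under Planned statistical analysis, apart from the sample size.

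- **Locomotion.** Joint reaction forces of the hip, knee and ankle are analysed by a two-way repeated-measures ANOVA with six gravity conditions and ten locomotion trials. Three effects can lead to Bonferroni-corrected post-hoc t-tests: gravity, trial, and "the interaction between simulated gravity condition and locomotion trial".
- **Plyometrics.** The same forces are analysed by a one-way repeated-measures ANOVA with gravity as the only factor.
- **Level.** "Statistical significance will be assumed at p < 0.05".
- **Normality check.** "Normality of the data will be assessed via Kolmogorov-Smirnov testing", supplemented by looking at QQ plots and histograms. The article does not say whether the critical values allow for an estimated mean and SD, to which values the test is applied, or what happens when test and plots disagree.
- **Fallback.** "if data has a non-normal distribution the non-parametric Friedman test" with Dunn's post-test replaces the ANOVA. The sentence covers both designs.
- **Number of participants.** The Sample size section derives 21 participants and sets a target of 26.

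**The concern.** Friedman's test ranks the conditions within each participant and compares rank sums across one set of conditions. It has no second factor and no interaction term. The sentence that names it follows both ANOVA specifications and makes no exception for the two-way one. If locomotion forces are judged non-normal, the stated rule therefore replaces a two-factor analysis with a one-factor test.

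What is lost is the comparison of gravity effects between gaits and speeds. The Introduction gives that comparison weight: it reports different preferred gaits at different gravity levels, and muscle-tendon behaviour at 0.7g that was preserved in walking but not in running.

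Whether the loss occurs depends on a normality check whose result can change with software defaults and with an unstated weighing of test against plots.

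**Working it through.** **1. Number of participants at which the trigger operates.** The article gives "t-test (matched pairs), α = 0.05, Power = 0.95, two-tailed" and n = 21, but no effect size (it refers to a supplementary file that is not shown), so 21 cannot be reproduced forwards. Solved backwards with the noncentral t distribution, n = 21 at 95% power implies a standardised paired difference of 0.828. The target follows from 21 × 1.25 = 26.25, stated as 26. With 25% lost, 26 × 0.75 = 19.5 remain. The check would thus run on about 20 to 26 participants.

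**2. Size of the locomotion design.** Table 1 marks 3 walking, 2 skipping and 5 running trials: 3 + 2 + 5 = 10. Six gravity levels give 6 × 10 = 60 cells, and the interaction has (6 − 1) × (10 − 1) = 45 degrees of freedom.

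**3. What Friedman can test in that layout.** Simulated data, n = 21, 800 runs per row:

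force = participant effect (SD 1) + residual (SD 1) + *a* × g × t,

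where g and t run evenly from −1 to 1 over gravity levels and trials. There is an interaction but no main effect. The values of *a* are assumptions. Rejection rates at 0.05:

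| *a* | ANOVA interaction | Friedman, gravity means | Friedman, trial means | Friedman, all 60 cells |
|---|---|---|---|---|
| 0 | 4.0% | 4.6% | 5.4% | 3.5% |
| 0.3 | 61% | 5.1% | 5.5% | 49% |
| 0.6 | 100% | 4.5% | 3.5% | 100% |

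On averaged data Friedman stays near 5% however strong the interaction is. Over all 60 cells it does react, but with purely additive effects (slope 0.5 for each factor, no interaction, 300 runs) it also rejected in 100% of runs. It therefore does not isolate the interaction. Running Friedman separately within each of the ten trials would give ten tests of gravity and no test of whether the gravity effect differs between trials.

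**4. How the trigger behaves.** Rejection rates at a nominal 5% for n = 21 / n = 26, with mean and SD estimated from the sample. There were 5,000 samples per case (3,000 for Shapiro-Wilk). The distributions are assumptions.

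| Distribution | KS, standard critical values | KS, Lilliefors | Shapiro-Wilk |
|---|---|---|---|
| Normal | 0.0% / 0.0% | 4.6% / 5.1% | 4.9% / 5.5% |
| Lognormal, σ = 0.5 | 1.9% / 2.7% | 38% / 43% | 56% / 65% |
| Exponential | 4.7% / 8.3% | 61% / 72% | 85% / 94% |
| Lognormal, σ = 1 | 21% / 33% | 81% / 89% | 94% / 98% |
| t, 3 df | 3.5% / 4.8% | 28% / 30% | 36% / 42% |

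The difference comes from the critical value of the KS distance: 0.287 (standard) against 0.188 (Lilliefors) at n = 21, and 0.259 against 0.170 at n = 26. The standard version almost never rejects unless the skew is extreme. The Lilliefors version holds its size but has less power than Shapiro-Wilk for every non-normal shape in the table.

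**The case against.** The strongest reply is that this is a conditional fallback. The planned locomotion analysis does test the interaction, with a sphericity correction, and no stated figure or main analysis is wrong. The section also words the locomotion question as the effect of gravity on joint loading, and Friedman over six gravity levels still tests a gravity effect. Both points stand and limit the consequence. They do not make Friedman fit a two-factor design whose interaction the section itself lists.

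Several stronger readings are tempting, and the article does not support them:

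- *The normality test does not work at this sample size.* That holds only for the uncorrected version, and the article does not say which is meant. Nor is the test the sole trigger, since plots accompany it. If the uncorrected version is used, the test alone would rarely cause the switch, and the loss would depend mainly on the visual judgement.
- *A false alarm is almost certain.* The sum 1 − 0.95^60 = 0.954 assumes cell-by-cell testing, independent cells and one flag being enough to switch. The article states none of these, and independence is implausible for repeated measures on the same people.
- *The plan tests raw forces instead of residuals.* The text does not say how the check is applied. Within a single cell the two differ only by a constant; they differ if values are pooled over cells.
- *The fallback discards incomplete participants.* Classical repeated-measures ANOVA has the same limitation, so this does not count against the fallback.
- *The primary analysis is affected.* Joint reaction forces are the primary outcome, but two analyses address them and neither is labelled primary. In the plyometric one, Friedman matches the design.

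The version of the test might be settled in a fuller plan. The choice of Friedman for the two-way design is stated, so it would have to be replaced there, not merely filled in.

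**Conclusion.** The point holds for the locomotion analysis. If the fallback is used as written, the 45-degree-of-freedom interaction is not tested. This follows from the structure of Friedman's test and does not depend on the simulation, which only illustrates it under assumed effect sizes and normal errors.

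The trigger is a secondary weakness, best described as weak and under-specified. For one assumed skewed distribution (lognormal, σ = 0.5) at n = 21 to 26, the choice of critical values alone moves the rejection rate from about 2–3% to 38–43%. How likely the switch is in this study cannot be said, because the article gives no distribution for the forces and no rule for combining test and plots.

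The planned ANOVA, the sample size and the plyometric fallback are untouched by this point. It should be settled before the data are analysed, because a fallback chosen afterwards would be data-driven.

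**What to change.** For the locomotion analysis, replace Friedman with a fallback that keeps gravity, trial and their interaction. Any one of these would serve, named in advance:

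- a two-factor mixed model on log force, provided the force measure is strictly positive (Table 4 gives the unit but does not say whether the measure is a magnitude or a signed component);
- an aligned-rank-transform ANOVA;
- a participant-level permutation or bootstrap test of the same three terms.

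Judge normality on the model residuals, mainly by QQ plot. If a formal test is kept, name it and its version, and say how it is weighed against the plots. Friedman with Dunn's post-test may stay for the one-way plyometric analysis.

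The cost is analysis-plan wording: no extra participants, measurements or changes to the sessions. There is a small downside, in that effects on a log or rank scale are read differently from differences in newtons, so the plan should say how they will be reported.

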### Data management

Protection of all personal information collected throughout the experiment is ensured compliance with GDPR requirements:

Data will be collected by the L.O.O.P. GBF personnel on an encrypted laptop and stored on a secure server, anonymized, backed up and then shared according to a data sharing agreement to the partners using an encrypted file sharing system. Therefore, all data files will be named with a key identifier that L.O.O.P. personnel will define and have responsibility to manage securely.The ‘raw’ kinematics, kinetics, and electromyography data will be saved in the Vicon 3D-Motion Capture System as.C3D files whilst ultrasound data will be saved in DICOM format. Both sets of files will be temporarily stored on encrypted data capture laptops. All files will be pseudonymised with a numeric code and kept separate from all other study data in a password protected folder.The ‘raw’ data will be uploaded on the same day of the data collection to a shared drive on a secure server by L.O.O.P. personnel. Access will be shared with the researchers from other institutions. A secured connection will be used to upload and download raw data from the shared drive. All academic partners will be able to access and download the data from this shared area and perform the analysis or calculation independently.As a number of institutions will be involved in the project, a data sharing agreement between institutions will be obtained but only pseudonymised data will be shared.

### Timeline

Depending on the current Covid restrictions, recruitment of participants will begin on November 1^st^, 2022 and is expected to be completed by March 31^st^, 2023.

### Summary

This study describes a protocol for the first time where a unique vertical body weight support system will be used to simulate, in high-fidelity, several locomotor and plyometric movements at a variety of gravity levels, including those resembling Lunar (0.16g) and Martian (0.38g) gravities. To our knowledge, this will be the first time such a facility has been used to simultaneously collect state-of-the-art movement kinetics, kinematics, muscle activation and muscle-tendon behaviour in a range of hypogravity conditions. Using these data as inputs within a computational musculoskeletal modelling and optimisation framework, we will estimate lower limbs internal kinetics (i.e., joint reaction forces) which is critical to gain a better understanding and prediction of hypogravity-induced musculoskeletal adaptations. Integration of muscle-tendon behaviour within the musculoskeletal modelling will significantly advance the understanding of the importance of forces generated through muscular contractions for preserving musculoskeletal health in low gravity environments. Such insights on the relationship between movement in hypogravity and internal loads will be key to inform on future mitigation strategies and prevention of detrimental adaptations due to prolonged exposure to hypogravity but will also be crucial to guide Lunar surface extravehicular activity (EVA) operations, and EVA suit and habitat ergonomics.

## Conclusion

The results of the study will provide the first estimations of internal musculoskeletal loads associated with human movement performed in a range of hypogravity levels. This will be achieved through the collection of state-of-the-art kinetics, kinematics, muscle activation and muscle-tendon behaviour and its integration within a musculoskeletal modelling and optimisation framework. Thus, our unique data will be a key step towards modelling the musculoskeletal deconditioning associated with long term habitation on the Lunar surface, and thereby aiding the design of Lunar exercise countermeasures and mitigation strategies, while also guiding Lunar surface extravehicular (EVA) operations, and EVA suit and habitat ergonomics.
